### Outcomes

2.7

#### Primary endpoint

2.7.1

The primary endpoint of this study is the occurrence of ATs at 1 year with a blanking period of 90 days after ablation.

#### Secondary endpoints

2.7.2

The key secondary endpoints are as follows:
The success rate of the PVITotal procedural timeLA dwelling timeTotal fluoroscopy timeRadiation exposureComplication rateOccurrence of ATs at 3 years after ablationComposite of all‐cause mortality or HF hospitalizations at 1 and 3 years after ablationAll‐cause mortality at 1 and 3 years after ablationHF‐hospitalizations at 1 and 3 years after ablationCardiovascular mortality at 1 and 3 years after ablationCardiovascular events at 1 and 3 years after ablationChange and percentage change in LVEF at 1 and 3 years after ablationChange and percentage change in QoL at 1 and 3 years after ablationOccurrence of ATs at 1 and 3 years after the latest ablation

### Other variables

2.8

Change and percentage change in brain natriuretic peptide at 1 and 3 years after ablationChange in NYHA functional class at 1 and 3 years after ablationChange in LV diastolic/systolic diameter, LA diameter, tissue doppler index E/e' at 1 and 3 years after ablationChange and percentage change in AF burden at 1 and 3 years after ablationChange and percentage change in serum creatinine, estimated creatinine clearance, estimated glomerular filtration rate at 1 and 3 years after ablationChange and percentage change in LA mean pressure before and after procedurePerioperative volume of infusion and urineInteraction between ablation outcome and LVEF, LV diastolic/systolic diameter, LA diameter, tissue doppler index E/e', serum creatinine, estimated creatinine clearance, estimated glomerular filtration rate, LA mean pressure before and after procedure, and patient characteristics at baseline

### Sample size

2.9

The estimated sample size is 110 (55 in each group). The sample size was calculated based on the primary hypothesis. The recurrence rate of ATs after an ablation of AF has been reported to be comparable between the CB and RF ablation in patients without HF, ranging 65%‐90%,^11^, ^12^, ^19^, ^20^ and the recurrence rate of ATs after CB ablation in patients with HF with an LVEF ≤40% has been reported to be equal to those without HF.^21^ Therefore, we hypothesized that the incidence of recurrent ATs after an ablation procedure could be 20% in the AF patients from previous studies in both the CB and RF ablation groups. The sample size for the randomized comparison was calculated as 51 patients per group with a power of 80% by a two‐sided 95% confidence interval for the difference in the population proportions with a width that is equal to 0.35 when the two estimated group sample proportions are equally 0.20. To cope with a potential loss‐to‐follow‐up, a minimum of 55 patients per group will be enrolled in the study. Withdrawn patients will not be replaced.

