### Study design

2.2

The CRABL‐HF study is designed as a prospective, multicenter, open‐label, controlled, and randomized, noninferiority clinical trial comparing the efficacy and safety of AF ablation at 1 year with a blanking period of 90 days after ablation between CB and RF ablation in patients with HF from 25 April 2018 to 31 March 2027 (Figure 1). The enrollment period is from 25 April 2018 to 31 March 2023. Eligible subjects will be randomly assigned to either the CB ablation or RF ablation group (allocation rate 1:1). The randomization will be stratified by the LA diameter. The study period will be extended if the number of enrollments is not be achieved during the period.

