### Randomization and allocation factor

2.10

The CRABL‐HF will consist of 110 patients at multicenter in Japan. The patients will be registered and randomly assigned to either the CB ablation or RF ablation group with a 1:1 allocation. We will use the minimization method proposed by Pocock and Simon to allocate the patients with an in‐house validated mail‐based system. Randomization will be stratified by the LA diameter, which may influence the evaluation of the efficacy of the ablation procedure,^22^ providing a balanced treatment assignment in both cohorts (<50 vs ≥50 mm). The patients' group allocations will be revealed to the operator at least 1 day before the ablation procedure. The information regarding the number of allocated subjects in each group will not be disclosed to the principal investigator or investigator until the completion of the study.

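### The 80% power attached to 51 patients per group does not follow from the stated calculation, which fixes only the width of a confidence interval

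*Protocol article*

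**What the plan says.** Section 2.2 (Study design) describes a "controlled, and randomized, noninferiority clinical trial comparing the efficacy and safety of AF ablation at 1 year". Section 2.7.1 defines the outcome: "The primary endpoint of this study is the occurrence of ATs at 1 year with a blanking period of 90 days after ablation".

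Section 2.9 (Sample size) says that the size rests on the primary hypothesis and was "calculated as 51 patients per group with a power of 80" per cent. The method named in the same sentence is a two-sided "95% confidence interval for the difference in the population proportions with a width that is equal to 0.35", evaluated "when the two estimated group sample proportions are equally 0.20". Enrolment is then raised to 55 per group, 110 in all, to allow for losses to follow-up.

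The article states no noninferiority margin and no alternative difference.

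**The concern.** Power is the probability of reaching a defined conclusion under a defined truth. For a noninferiority comparison it needs a margin, a significance level and assumed rates. A calculation aimed at interval width needs only the rates, the confidence level and the target width. Section 2.9 describes the second kind and reports a property of the first.

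The design section says noninferiority and section 2.9 ties the size to the primary hypothesis. A reader or an ethics board will therefore take the sentence as an 80% chance of showing that cryoballoon is noninferior to radiofrequency ablation. If the figure has no basis in the calculation, that reassurance is unfounded, and it could colour how an inconclusive result is later read.

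**Working it through.** **Inputs.** Recurrence 0.20 in both groups, two-sided 95% interval, total width 0.35 and 51 per group, all from section 2.9; 1:1 allocation from section 2.10. The variance term is 2 × 0.2 × 0.8 = 0.32.

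**Step 1: reproduce 51.** The continuity-corrected interval has total width

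2 × [1.96 × √(0.32/n) + 1/n].

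- n = 50: 2 × (0.1568 + 0.0200) = 0.3536, too wide.
- n = 51: 2 × (0.1552 + 0.0196) = 0.3497, which meets 0.35.

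So 51 is the smallest n that meets the target. The formula contains no power term. Other intervals do not give 51: uncorrected Wald, Newcombe and Agresti-Caffo each give 41, and corrected Newcombe gives 48. Reading 0.35 as a half-width gives 11 to 16.

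**Step 2: look for a reading of the stated inputs under which 51 per group has 80% power.** Noninferiority power is Φ(margin/SE − 1.96), with SE = √(0.32/51) = 0.0792. One-sided 2.5% matches the two-sided 95% interval.

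| Reading, 51 per group | Result |
|---|---|
| Half-width 0.175 as margin | Φ(2.209 − 1.96) = 60% (exact binomial 60%) |
| The same, with the continuity correction | Φ((0.175 − 0.0196)/0.0792 − 1.96) = 50% (exact 51%) |
| Full width 0.35 as margin | Φ(4.419 − 1.96) = 99% |
| Chance that the observed corrected width is at most 0.35 | 54% |
| The same, uncorrected width | 98% |

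A superiority reading would need about 20% against 46%, which contradicts the equal rates assumed. None of these gives 80% from the stated inputs.

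**Step 3: for scale, the margin at which 80% would be true.** Margin = (1.960 + 0.842) × √(0.32/n), at one-sided 2.5% and 20% in both groups.

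- 51 evaluable per group: 2.802 × 0.0792 = 0.222.
- The same with the continuity correction: 0.222 + 1/51 = 0.242.
- All 55 per group evaluable, uncorrected: 2.802 × √(0.32/55) = 2.802 × 0.0763 = 0.214.

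A margin of 22 points would tolerate about 42% recurrence against 20%.

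**Step 4: power at two illustrative margins** (one-sided 2.5%, 20% in both groups, no continuity correction).

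| Margin | 51 per group | 55 per group |
|---|---|---|
| 17.5 points | 60% | 63% |
| 20 points | 71% | 75% |

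**The case against.** Four points can be made for the plan.

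*The article is condensed, and the full protocol may state a margin.* This stands, and the absence of a margin here is not itself the finding. But section 2.9 sets out method, confidence level, width, rates and result in one sentence, and the power it reports is not a product of that calculation. That is a misstatement, not an omission.

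*Another set of inputs could give nearly the same size.* A 20-point margin at one-sided 5% with 80% power needs 50 per group. That is close, but neither that margin nor that level appears in the article, which specifies a two-sided 95% interval and a width that reproduces 51 exactly.

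*The 80% might mean the chance of achieving the target width.* With 55 per group, the chance that the corrected observed width is at most 0.35 is 81%. But the text attaches 80% to 51, where that chance is 54%, and explains 55 by losses to follow-up.

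*The 22-point margin is not unique.* This also stands. It assumes one-sided 2.5%, 51 evaluable per group and no continuity correction; Step 3 shows a range of 21 to 24 points, and at one-sided 5% the margin is 19.7 points. It is a yardstick, not the plan's margin.

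A reader might infer that the trial's real power is 50% or 60%, or that it recruits too few patients. The documents do not support this. The 17.5-point margin is only the half-width read as a margin, the aim in section 2.1 is worded as a comparison, and section 2.12 names a log-rank test for time-to-event outcomes. Without a stated margin, the 80% has nothing to refer to, and no other single figure can be put in its place.

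**Conclusion.** The point holds as a mislabelled claim. The number 51 is correct for what was calculated: a continuity-corrected 95% interval of ±17.5 points at 20% recurrence in both groups. The 80% is not a property of that calculation and cannot be recovered from its stated inputs. The reproduction of 51 needs only those inputs plus the continuity correction, which is inferred from the exact match. The margins of 21 to 24 points rest further on one-sided 2.5% and true rates of 20% in both groups.

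The sentence should be corrected because it is the article's only power statement and the trial is labelled noninferiority. It does not show that the enrolment target is wrong.

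**What to change.** In section 2.9, delete the clause giving 80% power and state what was calculated, for example: *With 51 evaluable patients per group and 20% recurrence in both, the continuity-corrected 95% CI for the difference has total width 0.35 (±17.5 points).*

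If a power statement is kept, give the margin and one-sided alpha it refers to, the evaluable number per group, and the power achieved under those choices. The Step 4 figures can serve only if that margin and method are the ones adopted, and those for 51 per group must not be reported as the power at 110 patients.

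The cost is wording only. Enrolment stays at 110. The drawback for the sponsor is that the stated power disappears or becomes less favourable.

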### Randomization and allocation factor

2.10

The CRABL‐HF will consist of 110 patients at multicenter in Japan. The patients will be registered and randomly assigned to either the CB ablation or RF ablation group with a 1:1 allocation. We will use the minimization method proposed by Pocock and Simon to allocate the patients with an in‐house validated mail‐based system. Randomization will be stratified by the LA diameter, which may influence the evaluation of the efficacy of the ablation procedure,^22^ providing a balanced treatment assignment in both cohorts (<50 vs ≥50 mm). The patients' group allocations will be revealed to the operator at least 1 day before the ablation procedure. The information regarding the number of allocated subjects in each group will not be disclosed to the principal investigator or investigator until the completion of the study.

### Data quality control and management

2.11

The principal investigator will authorize access to the electronic Case Report Form (CRF) system for investigators. The principal investigator will take full responsibility for the accuracy and reliability of all the data entered in the CRFs. The principal investigator and other investigators must not disclose the information contained in the CRFs to third parties. Only investigators can access data.

### Statistical analysis

2.12

Comparisons between the randomized groups will be performed on the basis of the intention‐to‐treat (ITT) principle. A per‐protocol basis analysis will also be performed to assess the robustness of the conclusions derived from the ITT basis analysis. The Kaplan‐Meier method will be used to estimate the survival curve, and the log‐rank test will be used to compare the curves between the groups for the time‐to‐event variables. Categorical variables will be analyzed using a chi‐square test or Fisher's exact test. Continuous variables will be presented as the mean ± standard deviation or median with the interquartile range (25th‐75th percentiles) and compared with the Student's t test or Wilcoxon rank‐sum test, as appropriate. A *P* value < .05 will be considered significant. Up‐to‐date versions of JMP (SAS institute) will be used to conduct analyses. The patient demographic data and outcome of catheter ablation in each group will be collected descriptively as presented in Tables 1 and 2.

**Table 1 joa312322-tbl-0001:** Patient characteristics at baseline

Age, years, n (%)
Male sex, n (%)
Height, cm
Weight, kg
NYHA functional class
History of a heart failure hospitalization
Number of heart failure hospitalizations
Blood pressure, mm Hg
Heart rate, /min
Duration of atrial fibrillation, months
Congestive heart failure, n (%)
Hypertension, n (%)
Diabetes mellitus, n (%)
Stroke and/or transient ischemic attack, n (%)
Structural heart disease, n (%)
Coronary artery disease
Valvular heat disease
Dilated cardiomyopathy
Hypertrophic cardiomyopathy
Others
Postopen heart surgery
CHADS_2_ score
CHA_2_DS_2_‐VASc score
Echocardiographic data
Left ventricular ejection fraction, %
Left atrial dimension, mm (%)
Left atrial dimension, <50 mm
Left atrial dimension, ≥50 mm
Computed tomography data
Pulmonary vein diameter, mm
Cardiac implantable electronic device
Pacemaker
ICD
CRT‐P
CRT‐D
History of anti‐arrhythmic drug use, n (%)
Disopyramide, n (%)
Cibenzoline, n (%)
Aprindine, n (%)
Pilsicainide, n (%)
Flecainide, n (%)
Propafenone, n (%)
Bepridil, n (%)
Sotalol, n (%)
Amiodarone, n (%)
Verapamil, n (%)
Beta‐blocker, n (%)
Digitalis, n (%)
Others, n (%)
Laboratory data

**Table 2 joa312322-tbl-0002:** The ablation procedure and complications

Procedure time (groin puncture to catheter extraction), min
Left atrial dwelling time
Fluoroscopic time, min
For cryoablation
Total freezing cycles, n
Total freezing time, s
The need for touch up RF ablation, n
For RF ablation
Total RF application time, s
Other adjunctive ablation, n (%)
Use of 3D mapping system, n (%)
Complications, n (%)
Pericardial effusion requiring drainage
Pericardial effusion not requiring drainage
Transient ischemic attack
Cerebral infarction
Other thromboembolisms
Transient phrenic nerve paralysis
Prolonged phrenic nerve paralysis
Severe pulmonary vein stenosis
Hematoma at the puncture site
Pseudoaneurysm at the puncture site
Gastric hypomotility
Others
Death
Discharge prescription, n (%)
Oral anticoagulant
Vitamin‐K antagonist
Direct oral anticoagulant
Antiarrhythmic drugs
Disopyramide
Cibenzoline
Aprindine
Pilsicainide
Flecainide
Propafenone
Bepridil
Sotalol
Amiodarone
Verapamil
Beta‐blocker
Digitalis
Others
Angiotensin converting enzyme inhibitor
Angiotensin II receptor blocker
Angiotensin receptor‐neprilysin inhibitor
Mineralocorticoid Receptor Antagonists
Ivabradine
Loop diuretic
Statin

Abbreviation: RF, radiofrequency.

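### Allocation is balanced on LA diameter, but the tests named in the analysis section take no account of it: a small, avoidable loss of precision

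*Protocol article*

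**What the plan says.** All references are to the protocol article.

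- **Allocation.** Section 2.2 says randomization is stratified by LA diameter. Section 2.10 gives the method, "We will use the minimization method proposed by Pocock and Simon to allocate the patients", in a 1:1 ratio, with a cut at 50 mm. LA diameter is the only factor named. The reason given is: "Randomization will be stratified by the LA diameter, which may influence the evaluation of the efficacy of the ablation procedure".
- **Analysis.** Section 2.12 describes Kaplan-Meier curves and says that, for time-to-event variables, the log-rank "test will be used to compare the curves between the groups". Categorical variables get a chi-square or Fisher's exact test. None of these is described as stratified or adjusted, and the section does not say which of them is the primary comparison.
- **Other uses of LA diameter.** It appears as a baseline row in Table 1, already split at 50 mm. Section 2.8 also lists it among the other variables, as a change from baseline and as an interaction item. None of these adjusts the primary comparison.
- **Sizing.** Section 2.9 sizes the trial on an unadjusted difference between two proportions of 0.20.

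**The concern.** When arms are balanced on a prognostic factor, the variation between its strata no longer contributes to chance differences between the arms. A test that ignores the factor still counts that variation in its standard error. The nominal standard error is then larger than the true one, the interval is wider than it needs to be, and the test rejects less often than its nominal level.

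This matters here because the trial has 110 patients, is described as a noninferiority trial in Section 2.2, and is sized on the width of one confidence interval. In that setting excess width lowers the chance of a conclusive answer. The LA stratum is known for every patient at allocation, so using it costs nothing.

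**Working it through.** **Inputs from the article:** 51 evaluable and 55 enrolled patients per group; 20% recurrence in both groups; two-sided 95% interval of width 0.35 (half-width 0.175); significance at 0.05; 1:1 allocation balanced on LA diameter at 50 mm.

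**Inputs not in the article, so assumed:** share f of patients with LA of 50 mm or more, 10% to 50%; recurrence risk ratio RR for large versus smaller LA, 1.5 to 3.

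**Step 1. The plan's own figure.** With a continuity-corrected Wald interval, width = 2 × [1.96 × √(2 × 0.2 × 0.8/n) + 1/n]. This gives 0.3536 at n = 50 and 0.3497 at n = 51, so 51 per group is reproduced. Without the correction n would be 41. The sizing calculation contains no LA term.

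**Step 2. Variance with and without the stratum.** Keep overall recurrence at 0.20:
- p_low = 0.2/(1 − f + f × RR) and p_high = RR × p_low
- within-stratum variance W = (1 − f) × p_low(1 − p_low) + f × p_high(1 − p_high)
- variance ratio r = W/0.16
- overstatement of the standard error = 1/√r − 1
- true two-sided error at nominal 5% = 2 × [1 − Φ(1.96/√r)]

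Worked case, f = 0.3 and RR = 2: p_low = 0.2/1.3 = 0.154 and p_high = 0.308. W = 0.7 × 0.154 × 0.846 + 0.3 × 0.308 × 0.692 = 0.155, so r = 0.969 and the standard error is overstated by 1.6%.

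**Step 3. Power to exclude a difference of 0.175 at 51 per group.** The value 0.175 is half the planned width. I use it as a yardstick; the article does not state it as a margin. With SE_nom = √(0.32/51) = 0.0792 and SE_true = √(2W/51):
- unadjusted: Φ[(0.175 − 1.96 × SE_nom)/SE_true]
- adjusted: Φ[0.175/SE_true − 1.96]

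The widths below are Wald widths without continuity correction; the unadjusted width is 0.3105 throughout.

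| f | RR | SE overstated | True error | Adjusted width | Power, unadjusted | Power, adjusted |
|---|---|---|---|---|---|---|
| 0.1 | 1.5 | 0.26% | 4.94% | 0.3097 | 59.9% | 60.1% |
| 0.3 | 1.5 | 0.50% | 4.89% | 0.3090 | 59.9% | 60.3% |
| 0.1 | 2 | 0.94% | 4.79% | 0.3076 | 59.9% | 60.7% |
| 0.3 | 2 | 1.59% | 4.65% | 0.3056 | 60.0% | 61.2% |
| 0.1 | 3 | 3.28% | 4.29% | 0.3007 | 60.2% | 62.6% |
| 0.3 | 3 | 4.37% | 4.08% | 0.2975 | 60.3% | 63.5% |

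The cases with f = 0.2 and f = 0.5 fall within the same range. Over the whole grid the power lost is 0.2 to 3.3 points.

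**Step 4. Log-rank simulation.** Settings: 110 patients; one-factor minimization favouring the under-represented arm with probability 0.8; exponential event times censored at 1 year; no blanking period and no loss to follow-up; 6,000 runs per setting. The hazard ratio of 2.5 is assumed and has no source in the article. Monte Carlo standard error is about 0.3 points for the null rates, √(0.045 × 0.955/6000), and about 0.6 points for power, √(0.74 × 0.26/6000).

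| f | RR | Null rejection, unstratified / stratified | Power at HR 2.5, unstratified / stratified |
|---|---|---|---|
| 0.2 | 1.5 | 4.8% / 4.9% | 74.9% / 75.1% |
| 0.3 | 2 | 4.5% / 4.7% | 73.2% / 74.8% |
| 0.5 | 2 | 4.6% / 4.7% | 73.1% / 74.7% |
| 0.3 | 3 | 4.25% / 5.3% | 68.2% / 73.5% |

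A separate run with no LA effect, and one third of patients with large LA, gave 74.6% and 74.4%. Stratifying therefore costs essentially nothing if the factor turns out not to matter.

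**Step 5. An extreme bound.** With recurrence of 10% versus 50% (RR = 5) and f = 0.25, W = 0.75 × 0.09 + 0.25 × 0.25 = 0.13, r = 0.8125, and the standard error is overstated by 11%.

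**The case against.** The best reply has four parts.

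- **The size rests on assumptions.** The article says only that LA diameter "which may influence the evaluation of the efficacy of the ablation procedure" and gives no effect size or prevalence. This stands, and it is why a range is shown. A reader might infer that the plan treats LA diameter as an established predictor of recurrence; the text does not go that far.
- **The cost is small for moderate effects.** This stands. At a risk ratio of 2 or less, the standard error is overstated by under 2% and the power loss is about 2 points or fewer. A reader might infer that the benefit of the allocation scheme is wasted. It is not: the balance between arms is kept whichever test is used, and only part of the gain in precision goes unclaimed.
- **A fivefold risk ratio would make the loss look large.** Sections 2.3 and 2.6.2 exclude LA above 55 mm, so the upper stratum spans only 50 to 55 mm. A fivefold contrast is hard to assume without support, and Step 5 should be read only as an outer bound.
- **Section 2.12 is a condensed paragraph.** It never says the tests are unstratified and does not name the primary one; the full protocol or SAP may already specify a stratified analysis. This lowers confidence but does not remove the point. Section 2.12 does name its methods, and none of those that could serve the primary endpoint uses the factor that Section 2.10 singles out.

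**Conclusion.** The point holds as a minor matter of efficiency. The analysis methods as stated leave out the one named allocation factor. If LA diameter is prognostic, the unadjusted interval is slightly too wide and the test mildly conservative.

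At 20% overall recurrence, with 10–50% of patients having large LA and a risk ratio of 1.5 to 3 (both assumed), the standard error is overstated by about 0.3–4.4%. True two-sided error is about 4.1–4.9%. The power lost is about 0–3 points for excluding a difference of 0.175, and about 0–5 points for a log-rank test at an assumed hazard ratio of 2.5. The loss becomes noticeable only when large LA roughly triples recurrence.

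A reader might infer that the mismatch makes the comparison invalid or raises the false-positive rate. It does neither: the error runs in the conservative direction, and 51 evaluable and 55 enrolled per group remain as stated. Confidence is good on the mismatch and its direction, and limited on its size.

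**What to change.** In Section 2.12, state that the primary comparison of AT recurrence at 1 year accounts for the LA stratum (below versus at or above 50 mm). Give a Mantel-Haenszel or stratum-weighted risk difference with its 95% confidence interval, and a log-rank test stratified by the same factor. Keep the unstratified result as a sensitivity analysis. With two strata and about 22 expected events (0.20 × 110), the adjustment is simple.

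The cost is one sentence. Table 1 already records LA diameter in these two categories, and the sample size does not change. The choice should be fixed before the outcome data are analysed so that it cannot depend on the results. If the full protocol or SAP already specifies a stratified analysis, the article's text needs only to be aligned with it.

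### LVEF and QoL changes are compared without using the collected baseline value, and each question is tested twice; the tests are valid but less efficient, most clearly for percentage change in LVEF.

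*Protocol article*

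**What the plan says.** Section 2.7.2 of the protocol article opens its list with "The key secondary endpoints are as follows". The list includes LVEF and QoL, each as a change and as a percentage change, each at 1 and 3 years.

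Section 2.12 gives one rule for comparing continuous variables between the randomized groups: they are "compared with the Student's t test or Wilcoxon rank‐sum test, as appropriate". Its threshold is that a P "value < .05 will be considered significant". No covariate is named.

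The baseline values will exist. Table 1 has a row for "Left ventricular ejection fraction", and a change in QoL cannot be computed without a baseline AFEQT score. Allocation does not balance either of them. Section 2.10 says "Randomization will be stratified by the LA diameter" (below 50 mm versus 50 mm or more) and names no other factor.

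Section 2.9 states: "The estimated sample size is 110 (55 in each group").

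**The concern.** A change score fixes the slope of follow-up on baseline at 1. If the true slope is below 1, patients who start low tend to rise more. A chance baseline difference between two groups of about 55 then passes into the cryoballoon versus radiofrequency contrast. Percentage change also divides by the baseline, which for LVEF is at most 40 in every patient, so those with the lowest values carry most weight in the mean and the variance.

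Listing both forms gives 2 endpoints × 2 time points × 2 forms = 8 tests for 4 questions. Nothing says which result stands if the two forms disagree.

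At stake are the precision and readability of two measures of benefit in a small heart failure trial.

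**Working it through.** **The plan's own figure.** Section 2.9 says: "The sample size for the randomized comparison was calculated as 51 patients per group with a power of 80"%. It is based on a two-sided 95% CI of width 0.35 at 20% in both groups. The continuity-corrected interval 2 × (1.96 × √(0.32/n) + 1/n) gives 0.3536 at n = 50 and 0.3497 at n = 51, so 51 reproduces. That figure serves the primary endpoint. No sample size, SD or correlation is stated for LVEF or QoL. I use 51 per group below; every SD, correlation (rho) and effect size is my assumption.

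**Precision against raw change.** With baseline SD s0 and follow-up SD s1, the large-sample ratio of ANCOVA variance to change-score variance is

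(1 − rho²) × s1² / (s0² + s1² − 2 × rho × s0 × s1).

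This never exceeds 1 and equals (1 + rho)/2 when the SDs are equal. Starting from 80% power for the change score, ANCOVA power is Φ(2.802/√ratio − 1.96).

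| s1/s0 | rho | variance ratio | ANCOVA power |
|---|---|---|---|
| 1 | 0.3 | 0.65 | 93.5% |
| 1 | 0.5 | 0.75 | 89.9% |
| 1 | 0.8 | 0.90 | 84% |
| 1.25 | 0.3 to 0.5 | 0.78 to 0.89 | 89% to 84% |
| 2 | 0.5 | 0.75 × 4/3 = 1.00 | 80% |

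In the last row the slope, rho × s1/s0, is exactly 1, so adjustment gains nothing.

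**Chance imbalance.** With equal SDs, a baseline difference d shifts the expected change contrast by −(1 − rho) × d. At 51 per group, one standard error of d is √(2/51) = 0.198 SD.

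| rho | shift at 1 SE of imbalance | SE of the change contrast |
|---|---|---|
| 0.3 | 0.14 SD | 0.23 SD |
| 0.5 | 0.10 SD | 0.20 SD |
| 0.8 | 0.04 SD | 0.13 SD |

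Given a 2 SE imbalance, the false-positive rate of the change-score test is about 17%, 13% and 8% at these three correlations. ANCOVA stays at 5%. Averaged over all randomizations, the change-score test also holds 5%.

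**Percentage change in LVEF, by simulation.** Setting: 51 per group, baseline mean 30, SD 6, truncated to 12-40, rho 0.5. The group difference (3.36 points at follow-up SD 6, 4.9 points at SD 10) gives raw change about 80% power. The mean LVEF rise common to both groups matters, so it was varied from 0 to 15 points.

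| follow-up SD | percentage change, rise 0 to 15 | raw change | ANCOVA |
|---|---|---|---|
| 6 | about 75% to 50% | about 80% | about 90% |
| 10 | about 78% to 66% | about 80% | about 80% |

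A second simulation used a baseline truncated to 15-40, residual SD 9, a 5-point effect and a follow-up-on-baseline slope of 0.4, 0.6 or 0.8. Power at those three slopes was:

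- ANCOVA: 79%, 80% and 79%
- t test on raw change: 74%, 77% and 79%
- t test on percentage change: 54%, 61% and 66%
- Wilcoxon on percentage change: 56%, 63% and 67%

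Type I error there was 4.6% to 5.2% for every method.

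**The case against.** **The planned tests are valid.** This stands. A reader might infer that they are biased or inflate false positives. They do not: type I error is about 5%, and raw change is unbiased over repeated randomization. The effect of imbalance is conditional on the sample obtained, and the planned standard error already allows for it on average. What remains is a choice of efficiency and of robustness to the imbalance actually seen.

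**The gain over raw change may be small.** This also stands. A reader might take the rise from 80% to 90% as the size of the loss. It requires equal SDs and rho 0.5. LVEF is capped at 40% on entry but not at follow-up, so a larger follow-up SD is plausible. Under such assumptions the second simulation gives a gain of only 0 to 5 points, and at an SD ratio of 2 with rho 0.5 it is zero.

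**The percentage-change loss is not one number.** It depends on the mean rise, which the documents do not give, so it must be stated as a range. Since raw change is also listed, the more precise measure is not lost; but nothing says it takes precedence.

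**QoL has less support.** The small-denominator argument comes from the LVEF criterion. No entry criterion restricts AFEQT, and QoL was not simulated. For QoL only the general argument for baseline adjustment holds.

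**A statistical analysis plan may add models.** It may, and the rule in section 2.12 is generic. But the article fixes both the endpoint form and the test, so this concerns a stated method and not an omission. The interaction item in section 2.8 asks about effect modification and does not adjust these comparisons.

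**Conclusion.** The point holds as one of efficiency and clarity in key secondary endpoints. The stated tests are valid, but they ignore a baseline that is already collected and in large samples can only match or fall short of the adjusted comparison.

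Against raw change, the gain runs from nothing (follow-up SD well above baseline SD) to 4-13.5 points of power from 80% (equal SDs, rho 0.8 to 0.3). Against percentage change in LVEF, the shortfall is clearer: from about 2 points (80 − 78) to about 40 points (90 − 50) across the assumed follow-up SDs and mean rises. Testing two forms of each endpoint with no rule of precedence is a defect whatever the correlation.

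The documents do not support a claim of invalid results, a single headline loss, or the same percentage-change loss for QoL. Extending the point to every change variable in section 2.8 would need its own argument. The primary endpoint and sample size are untouched.

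**What to change.** In section 2.12, state that follow-up LVEF and AFEQT at 1 and 3 years will be compared between groups by ANCOVA, with the baseline value and the LA diameter stratum (<50 versus ≥50 mm) as covariates. Report the adjusted mean difference with its 95% CI as the single comparison for each endpoint and time point, which leaves 4 comparisons in place of 8. Keep change and percentage change as descriptive summaries without tests.

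The cost is wording, one model fit per comparison and one degree of freedom per covariate. No new data, visits or patients are needed.
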